### 2.10. Study Endpoints

The study’s primary endpoint is the change from baseline of IBS-SSS at the first and the second follow-up. The co-primary endpoint is the rate of responders for each dietary intervention, defined by a ≥50-point reduction in IBS-SSS, which has been shown to be a clinically significant improvement [21,37], at the first and second follow-ups. Secondary endpoints measured at both follow-ups will include the rate of subjects reporting AR and changes in IBS-QoL, SF-12, HADS, and GSRS-IBS. Adherence to dietary intervention, use of rescue medications, rate of participants who achieve IBS-SSS < 175, discontinuation rate (and causes), and AE/SAEs comprise also secondary endpoints.

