### 2.11. Statistics

#### 2.11.1. Sample Size Calculation

The sample size was calculated at 108 participants (54 per group) with expected values taken from the meta-analysis of Varju et al. [38] and a pre-specified statistical power of 80%, significance level α = 0.05, and 10% adjustment for non-adherence to detect a significant improvement in the primary outcome measure 100 vs. 59 points (estimated standard deviation = 60) in the MED-LFD and NICE groups, respectively.

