#### 2.11.3. Statistical Analysis

Categorical variables will be presented as relative frequencies (%) and continuous variables as mean values (standard deviation) for those normally distributed and as median (interquartile range) for those not normally distributed. Normality will be evaluated graphically (i.e., using histograms, p-p plots, boxplots, q-q plots) and statistically through the Kolmogorov Smirnoff test. Student’s *t*-test will be used to examine differences in all quantitative variables and chi-squared test for all categorical variables between the two intervention groups (NICE vs. MED-LFD). Paired analysis will be utilized to compare all scores between baseline, first follow-up and second follow-up, independently, and also a test-for-trend will be performed to assess any potential longitudinal changes. For the data analysis, the statistical package STATA 16 will be used, and a *p*-value of ≤0.05 will be regarded as statistically significant.

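### Two primary endpoints at two follow-ups give four unadjusted tests, and no rule says which of them decides whether the trial succeeded

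*Protocol article*

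**What the plan says.** Section 2.10 of the protocol article gives the first endpoint and its two visits: "The study’s primary endpoint is the change from baseline of IBS-SSS at the first and the second follow-up". It then adds a second: "The co-primary endpoint is the rate of responders for each dietary intervention", with response set at a fall of at least 50 points in IBS-SSS, also assessed "at the first and second follow-ups". Two endpoints at two visits make four primary between-group comparisons.

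Section 2.11.3 assigns Student's t-test to quantitative variables and chi-squared to categorical ones. It gives one cut-off for all of them: a p-value of 0.05 or less "will be regarded as statistically significant". It states no order of testing, split of alpha or adjustment.

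Section 2.11.1 sizes the trial on one comparison of mean IBS-SSS change, 100 versus 59 points with SD 60, at "significance level α = 0.05" and 80% power. It names no visit and gives no expected responder rates.

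Section 2.9 places the first follow-up at 4 weeks in the NICE group and at the end of reintroduction in the MED-LFD group. Section 2.11.2 analyses responders in both ITT and PP, and IBS-SSS change in PP only.

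**The concern.** A confirmatory trial needs a rule that turns its primary tests into one conclusion. Here the endpoints and the threshold are both fixed, but the rule linking them is absent. Three readings fit the text: any of the four tests suffices, both endpoints must succeed at one visit, or all four must succeed. They have different operating characteristics, and none is identified as the plan's.

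Under the loosest reading, the trial could be called positive on whichever of four correlated tests reaches 0.05. That includes the two at a first follow-up whose timing differs between arms. Under the strictest reading, the stated 80% power does not describe the chance of success, because the sample size considers a single comparison of means.

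**Working it through.** **Inputs from the article.** Difference 100 − 59 = 41 points, SD 60, alpha 0.05, power 80%, 10% adjustment, 54 per arm (section 2.11.1); 1:1 allocation (section 2.4.1); response is a reduction of at least 50 points (section 2.10). Evaluable per arm: 54 × 0.90 = 48.6, taken as 49.

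**Assumptions not in the article.** Two-sided tests; normally distributed changes; the same means and SD at both visits; within-patient correlation between the two follow-up changes, shown as a range.

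**1. The plan's own sample size.** n per arm = 2 × (1.960 + 0.842)² × (60/41)² = 33.6, so 34. Then 34/0.90 = 37.8, so 38 per arm and 76 in total. The stated 108 is not reproduced. With 49 evaluable per arm, the single comparison of means has about 92% power: 41/(60 × √(2/49)) = 3.38, and Φ(3.38 − 1.96) = 0.92.

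**2. False-positive rate if any one of four tests suffices.** Four independent tests would give 1 − 0.95⁴ = 0.185. That figure does not apply, because the responder outcome is the same score cut at 50 points. The two test statistics at one visit correlate at about 0.70 to 0.80. Simulation with no group difference used 40,000 trials per setting, 49 per arm, SD 60 and a common mean change of 59, 80 or 100:

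| Between-visit correlation | Any of four at p ≤ 0.05 |
|---|---|
| 0 | 0.149 to 0.163 |
| 0.3 | 0.151 to 0.158 |
| 0.5 | 0.142 to 0.157 |
| 0.7 | 0.131 to 0.145 |
| 0.9 | 0.116 to 0.129 |

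**3. False-positive rate under other rules (same simulation).** Either endpoint at one named visit: about 0.08 to 0.09. Both endpoints at the same visit, with either visit allowed: about 0.03 to 0.045. All four required: 0.01 or less.

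**4. Power of the responder test.** Under normality the sizing inputs imply responder rates of Φ((100 − 50)/60) = Φ(0.833) = 0.798 and Φ((59 − 50)/60) = Φ(0.15) = 0.560. The mean rate is 0.679. With 49 per arm:

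- null standard error: √(2 × 0.679 × 0.321/49) = 0.0943
- alternative standard error: √((0.798 × 0.202 + 0.560 × 0.440)/49) = 0.0912
- power: Φ((0.238 − 1.96 × 0.0943)/0.0912) = Φ(0.58) = 0.72

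**5. Power if more than one test must succeed.** Simulated with 100 versus 59 and SD 60 at both visits, 49 per arm. Both endpoints at six months: about 71%. All four: about 53% at correlation 0.3, 55% at 0.5 and 61% at 0.9.

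**6. An equal split, 0.05/4 = 0.0125 per test.** Power for IBS-SSS change at 49 per arm is 0.81 by the normal approximation and 0.797 by the t-test, so about 80%. Responder power falls to about 52%.

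**The case against.** The strongest defence is that the article calls the responder rate co-primary, which often means that every such endpoint must succeed. On that reading alpha is not inflated at all. This stands as far as it goes: a reader might infer that the trial's error rate simply is about three times 0.05, and the article does not support that, because it never says that one success is enough. But it does not say that all are required either, nor how the two visits enter, and the all-must-succeed reading carries the power cost in step 5.

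A second defence is that a condensed article can leave multiplicity to an analysis plan. One may exist and may contain a hierarchy. But the article does more than stay silent: it fixes four primary comparisons and one threshold for all of them. Any hierarchy held elsewhere would have to be reconciled with that text.

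A third defence concerns the sample size. Two-sided alpha of 0.0125 with 80% power gives 48 per arm, and 48/0.90 = 53.3, so 54 per arm, exactly the stated number. A reader might infer an unstated four-way Bonferroni correction. The article states alpha 0.05, however, and 90% power at 0.05 comes almost as close (52 per arm). The match cannot be credited as a plan.

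Finally, the responder rates and the joint power figures rest on normality and on equal effects at both visits. Neither is in the article. They indicate size and are not properties the plan claims.

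**Conclusion.** The concern holds in conditional form. The defect is an undefined success rule across two endpoints and two visits, each tested at an unadjusted 0.05. Depending on the rule applied, the false-positive rate runs from 0.01 or less (all four required) to about 0.12 to 0.16 (any one suffices). The upper figures are about 2.3 to 3.2 times the stated alpha, over assumed between-visit correlations of 0 to 0.9.

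If all four are required, power is about 53% to 61% at 49 evaluable per arm, under the assumptions listed and correlation 0.3 to 0.9. The responder test alone has about 72%. The stated 80% therefore does not describe either the responder endpoint or joint success.

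The mismatch between 108 and the stated sizing inputs is a separate point and is not needed for this one.

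**What to change.** Name IBS-SSS change at six months as the single primary test at two-sided 0.05. Test the six-month responder rate next, also at 0.05, only if the first succeeds, and stop at the first p above 0.05. Make the first-follow-up comparisons secondary or place them last in the sequence. Label them first follow-up and not week 4, because the MED-LFD group has no IBS-SSS timepoint at 4 weeks (section 2.9). State one decisive analysis set for the primary test. Whether that should be ITT in place of the PP set that section 2.11.2 assigns to IBS-SSS change is a separate question.

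This order controls the error rate at 0.05 and leaves about 92% power for the primary test at 49 evaluable per arm on the article's inputs. It must be fixed before any between-group results are seen.

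The cost is a short paragraph across sections 2.10 and 2.11, with no extra participants. The downside is that fewer results can be claimed as confirmatory.

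An equal split at 0.0125 across the four tests also controls alpha and keeps about 80% power for IBS-SSS change, but leaves the responder test at about 52%. The fixed sequence is the better choice.

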### 2.11. Statistics

#### 2.11.1. Sample Size Calculation

The sample size was calculated at 108 participants (54 per group) with expected values taken from the meta-analysis of Varju et al. [38] and a pre-specified statistical power of 80%, significance level α = 0.05, and 10% adjustment for non-adherence to detect a significant improvement in the primary outcome measure 100 vs. 59 points (estimated standard deviation = 60) in the MED-LFD and NICE groups, respectively.

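### The stated sample size of 108 (54 per group) does not follow from the inputs given in section 2.11.1, which lead to about 78

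*Protocol article*

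**What the plan says.** Section 2.11.1 gives a total and a per-group number: "The sample size was calculated at 108 participants (54 per group"). The operating characteristics are "a pre-specified statistical power of 80%, significance level α = 0.05, and 10% adjustment for non-adherence". The effect is "100 vs. 59 points (estimated standard deviation = 60) in the MED-LFD and NICE groups", a difference of 41 points. The calculation is tied to the mean change in IBS-SSS, since its purpose is "to detect a significant improvement in the primary outcome measure 100 vs. 59 points". Sidedness is not stated, nor whether 60 is the SD of the change.

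Other sections supply the rest. Section 2.4.1 sets 1:1 allocation. Section 2.11.3 plans Student's t-test for quantitative variables and the chi-squared test for categorical ones, judged at 0.05, with no split of alpha. Section 2.11.2 analyses IBS-SSS change in the per-protocol population, and responders in both the intention-to-treat and per-protocol populations.

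Section 2.10 adds a second headline endpoint: "The co-primary endpoint is the rate of responders for each dietary intervention, defined by a ≥50-point reduction in IBS-SSS". Section 2.11.1 gives no responder rates and no power for it.

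**The concern.** A two-group comparison of means is fixed by difference, SD, alpha, power and allocation. The article gives all of these except sidedness, together with the inflation and the answer, and the answer is too large for the inputs. The size of the gap rules out rounding, so at least one figure is not the one used.

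The possible explanations describe different trials:

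- If SD 60 and 80% power were intended, about 30 more people are enrolled than the stated target needs.
- If the planning SD was larger, the published one is wrong. Taking larger SDs purely as assumptions, power for 41 points at 49 per group is about 80% at SD 72, 71% at SD 80 and 61% at SD 90.
- If alpha was divided among several primary comparisons, the 0.05 in sections 2.11.1 and 2.11.3 is not the planned threshold.

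A reader cannot tell which of these applies, and so cannot tell what the trial was designed to detect.

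**Working it through.** **Inputs.** Difference 100 − 59 = 41 points; SD 60; alpha 0.05, taken as two-sided because sidedness is not given; power 80%; 10% adjustment (all section 2.11.1). Allocation 1:1 (section 2.4.1). Student's t-test (section 2.11.3).

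**Attempt to reproduce 54 per group.**

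n per group = 2 × (z₀.₉₇₅ + z₀.₈₀)² × (SD/difference)²
= 2 × (1.960 + 0.842)² × (60/41)²
= 2 × 7.851 × 2.1416 = 33.6, so 34 by normal approximation.

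With the t distribution, power is 79.3% at 34 and 80.5% at 35 per group, so 35 are needed.

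Adjustment: 35/0.9 = 38.9, so 39 per group and **78 in total**. From 34: 34/0.9 = 37.8, so 38 per group and 76 in total. Multiplying by 1.1 instead of dividing by 0.9 gives the same rounded figures (38.5 to 39; 37.4 to 38).

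The stated 108 exceeds 78 by 30 participants (108/78 = 1.38).

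**Other readings of the stated inputs.**

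| Reading | Total |
|---|---|
| Two-sided, normal approximation | 76 |
| Two-sided, t-test | 78 |
| One-sided | 60 to 64 |
| Two-sided, inflated for a rank test | at most 92 |
| Stated in the article | 108 |

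No reading at alpha 0.05 and 80% power reaches 108.

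**Power that the stated number provides.** 54 × 0.9 = 48.6, so 48 or 49 evaluable per group. For 41 points at SD 60, two-sided 0.05:

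| Evaluable per group | t-test | Normal approximation |
|---|---|---|
| 49 | 91.7% | 92.3% |
| 54 | 94.0% | 94.4% |

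**What would make 54 come out.**

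- SD: 80% power at 48 to 49 evaluable needs an SD of about 71.0 to 71.7 (t-test), or 71.7 to 72.4 (normal approximation).
- Difference: at SD 60, about 34 points instead of 41.
- Alpha: 0.05/4 = 0.0125, as for two endpoints at two follow-ups, gives 48 per group by normal approximation, and 48/0.9 = 53.3, so 54. By t-test it gives 50, and 50/0.9 = 55.6, so 56.

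The article states none of these.

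**Responder rate, as a conditional side note.** Assume changes are normal with the stated means and a common SD of 60. The article does not say so. Then:

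- MED-LFD: P(change ≥ 50) = Φ((100 − 50)/60) = Φ(0.833) = 79.8%
- NICE: P(change ≥ 50) = Φ((59 − 50)/60) = Φ(0.150) = 56.0%

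The two-proportion test at two-sided 0.05 then has 72.0% power at 49 per group and 76.2% at 54. Mean and SD alone do not fix these rates. With the same means and SD, power at 49 per group under other shapes is about 53% (uniform), 54 to 63% (left-skewed), 78% (logistic), 82% (t with 5 degrees of freedom) and 80 to 97% (right-skewed gamma).

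**The case against.** The best defence is that a journal article condenses a longer document. An alpha split or a different SD may be recorded there, and the number enrolled may be well founded. That may be so, but it does not rescue the sentence as published, which gives inputs and a result that disagree. It is also fair to say that the mismatch errs towards more participants: on the stated inputs the mean-change comparison has more power than claimed. That limits the harm without removing the contradiction. Finally, the alpha 0.0125 explanation is conjecture, and it works only by normal approximation.

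A reader might go further and infer that the responder co-primary has 72% power where 80% was promised, so that the stated power is wrong for both headline endpoints. The document does not support this. Its 80% is attached to the difference in points, and it claims no power for responders. The 72% needs normally distributed changes, which are nowhere stated; other shapes span about 53% to 97%. It also uses 49 per group, whereas responders are analysed by intention to treat as well, where 54 per group gives 76% under the same assumption. A condensed article may also leave separate sizing of a co-primary endpoint to the full protocol. What remains is only a caution against reading the 80% as covering both endpoints.

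**Conclusion.** The inconsistency is established. On the stated inputs the requirement is 78 participants (76 by normal approximation), against 108 stated, and the stated number has about 92% power with 49 evaluable per group, or 94% with 54, not 80%. The result assumes a two-sided test; a one-sided test widens the gap. It does not depend on how the 10% adjustment is applied.

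This is an error of reporting or of an input, and which figure is at fault cannot be settled from the article. It does not show that the trial is too small for mean change. The responder figures of about 72% to 76% hold only under normality and are no more than a side note.

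**What to change.** Keep 108 and correct section 2.11.1 in one of two ways:

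1. Report the inputs actually used, so that 54 per group can be reproduced: the SD and whether it is the SD of change, alpha and any division of it, sidedness, power, and the allowance for non-adherence or attrition. If alpha was divided, bring the threshold in section 2.11.3 into line.
2. If SD 60 and two-sided 0.05 are right, state that 54 randomised and 49 evaluable per group give about 92% power for a 41-point difference.

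In either case, add a short sentence saying that the power statement concerns mean change only. If a power figure for the responder rate is wanted, give the assumed responder rates with it; the 72% should not be copied in as if the stated mean and SD determined it. Changing the rank of the responder endpoint is not called for on this ground and would be more than a wording change.

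The cost is a corrected paragraph, with no change to enrolment, endpoints or analysis. The exception is a divided alpha, where the significance threshold in section 2.11.3 must also be restated.

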#### 2.11.2. Study Populations

Intention-to-treat population (ITT) considers all randomized participants in the analysis, whether they complete the treatment as initially planned or not. Conversely, in the per-protocol (PP) analysis, we only analyze data from those who strictly adhere to the study protocol [39]. Responders (defined as participants with at least a ≥50-point reduction in IBS-SSS), AR rates, and the rate of participants who achieve IBS-SSS < 175 will be measured in the ITT and PP population; IBS-SSS, IBS-QoL, SF-12, HADS, GSRS-IBS change and use of rescue medications will be measured in the PP population. Discontinuation rate (and causes) and AE/SAEs will be measured in the ITT population.

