#### 2.4.1. Randomization

We have prepared a random allocation sequence using block randomization, with a 1:1 ratio of control to intervention group (block size *n* = 4). Participants will be informed that both diets may reduce their symptoms but diet masking is impossible.

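### The continuous primary endpoint (IBS-SSS change) is assigned to the per-protocol set only, which leaves the main comparison open to selection bias

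*Protocol article*

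**What the plan says.** Section 2.10 states: "The study’s primary endpoint is the change from baseline of IBS-SSS at the first and the second follow-up". It then adds a second top-level endpoint: "The co-primary endpoint is the rate of responders for each dietary intervention, defined by a ≥50-point reduction in IBS-SSS".

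Section 2.11.2 defines two analysis sets. For the first: "Intention-to-treat population (ITT) considers all randomized participants in the analysis, whether they complete the treatment as initially planned or not". For the PP analysis: "we only analyze data from those who strictly adhere to the study protocol". It then assigns the endpoints to sets one by one:

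- **ITT and PP:** responders, together with "AR rates, and the rate of participants who achieve IBS-SSS < 175 will be measured in the ITT and PP population".
- **PP:** "IBS-SSS, IBS-QoL, SF-12, HADS, GSRS-IBS change and use of rescue medications will be measured in the PP population".
- **ITT:** discontinuations with their causes, and AE/SAEs.

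The first two assignments stand in one sentence, so the contrast is explicit. No other section of the article gives an all-randomised analysis of IBS-SSS change.

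**The concern.** A set defined by strict adherence is chosen by what happens after randomisation. Several features of this trial could link that choice to outcome, and link it differently in the two arms:

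- Participants know their diet, since "diet masking is impossible" (section 2.4.1). For the whole cohort, adherence is a self-reported five-point answer given by telephone (section 2.8.3).
- The burdens differ. MED-LFD runs through restriction, reintroduction and personalisation (section 2.4.3 and its second and third phases). NICE is a four-week plan with free choice within food categories (section 2.4.2).
- Participants may leave because of symptoms that they cannot control (section 2.7).
- Only MED-LFD makes progress conditional on response: participants with adequate relief go on to reintroduction, and that arm's first follow-up falls at the end of reintroduction (sections 2.4.3 and 2.9).

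At stake is whether a superiority claim on the primary endpoint compares the groups that were randomised. The same restriction applies to IBS-QoL, SF-12, HADS, GSRS-IBS and rescue use. For rescue use it leaves out of the comparison any participant who departs with uncontrolled symptoms.

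**Working it through.** **Inputs from section 2.11.1:** improvement 100 against 59 points (difference 41), SD 60, α = 0.05 (taken as two-sided), power 80%, 10% allowance for non-adherence, 54 per group.

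**The plan's own figure.** n per arm = 2 × (1.960 + 0.842)² × 60² / 41² = 33.6, so 34 (35 by the exact t-test). With the 10% allowance, 34 / 0.9 gives 38 per arm, or 76 in total and not 108. This mismatch is a separate matter. The checks below take 54 per arm as planned.

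**Selection bias with no true difference.** Assume that PP membership follows a latent normal variable with correlation r to IBS-SSS improvement, and that the lowest fraction q of an arm is excluded. The mean improvement of those kept is then shifted upwards by

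r × SD × φ(z_q) / (1 − q),

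where z_q is the q-quantile of the standard normal. The factor φ(z_q) / (1 − q) is 0.195 for q = 0.10, 0.350 for q = 0.20 and 0.497 for q = 0.30. The false difference is the MED-LFD shift minus the NICE shift:

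| Excluded, MED-LFD vs NICE | r = 0.3 | r = 0.5 | r = 0.7 |
|---|---|---|---|
| 30% vs 10% | 5.4 | 9.1 | 12.7 |
| 20% vs 10% | 2.8 | 4.6 | 6.5 |
| 10% vs 10% | 0 | 0 | 0 |

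Example: 0.5 × 60 × (0.497 − 0.195) = 9.1 points. The first row is 13% to 31% of the planned 41 points. Swapping the two exclusion rates keeps the sizes and reverses the sign. The exclusion rates of 20% and 30%, their split by arm and the values of r are assumptions; the article gives only one 10% allowance, not split by arm.

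**Effect on the type I error.** For 30% against 10%, about 38 and 49 participants remain. The standard error is 60 × √(1/37.8 + 1/48.6) = 13.0. By normal approximation the nominal 5% becomes roughly 7%, 11% and 16% for the three values of r.

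**A second, simpler model.** If a fraction q of MED-LFD and nobody in NICE is excluded, and those excluded improve g points less than those kept, the false difference is q × g. For g = 60 and q = 0.10, 0.20, 0.30 this is 6, 12 and 18 points, with type I error about 8%, 16% and 29%. For g = 30 it is 3, 6 and 9 points, with about 6%, 8% and 11%. Equal 10% exclusion with an equal gap again gives zero.

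**Power if all randomised participants are analysed.** Two-sided t-test, 54 per arm, SD 60, scores available for everyone, and the difference shrunk by an assumed dilution:

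| Dilution | Difference | Power |
|---|---|---|
| none | 41 | 94% |
| 10% | 36.9 | 89% |
| 20% | 32.8 | 80% |
| 30% | 28.7 | 69% |

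At 30% dilution, 80% power needs about 70 per arm.

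**The case against.** The reading of section 2.11.2 is not in doubt. The case on the other side concerns scope, size and cost.

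- **Scope.** The responder co-primary, adequate relief and the rate below 175 points all have an ITT analysis, and discontinuations and adverse events are analysed in ITT. A reader might infer that the trial's main result as a whole is biased, or that it has no all-randomised evidence of efficacy. The article does not support that: one of the two primary endpoints is affected. Because responders are analysed in both sets, a gap between their ITT and PP results would also give some sign of selection. This stands.
- **Size and direction.** A reader might infer that the PP analysis must favour MED-LFD. That follows only if more poor responders are excluded there. Different burdens and the adequate-relief condition make this plausible, but the article does not say whether a MED-LFD participant who stays in the first phase counts as non-adherent. Under equal exclusion and equal correlations the bias is zero. This stands too, so the figures illustrate and do not predict.
- **Rescue use.** All rescue medication is recorded (section 2.6), and discontinuations with their causes are recorded (section 2.7) and analysed in ITT. Early leavers are therefore visible, although their rescue use is outside the planned comparison. This is a secondary endpoint and would not carry the point alone.
- **Cost.** It is tempting to say that an ITT analysis needs no more patients. That holds only up to about 20% dilution, and dilution can be harsher than a proportional shrinkage. If 10% of MED-LFD alone improved by zero, the difference would be 0.9 × 100 − 59 = 31 points and power 76%.
- **Detail that a SAP may hold.** The missing-data model, the sensitivity analysis and the adherence cut-off are commonly left to a SAP or full protocol, neither of which is shown. Their absence is not part of this point.

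None of this supplies an all-randomised analysis of the continuous primary endpoint. The article fixes the opposite.

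**Conclusion.** The point holds, limited to what section 2.11.2 assigns. IBS-SSS change, the other continuous scores and rescue use are analysed in the PP set only, although a dichotomy of the same IBS-SSS scores receives an ITT analysis and the article gives no reason for the difference. The comparison on the continuous primary endpoint is therefore not of the randomised groups and is liable to selection bias.

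That the assignment is made is certain from the text. The magnitude is conditional: from zero under equal exclusion to about 13 points under the most unequal case of the correlation model, and up to 18 points under the simpler model, all on assumed exclusion rates and outcome relations. The direction is open. Because the rule governs the primary endpoint and is cheap to change, it should be corrected before the analysis.

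**What to change.** In section 2.11.2, make all randomised participants, by assigned arm, the primary analysis set for IBS-SSS change, IBS-QoL, SF-12, HADS, GSRS-IBS change and rescue use. Keep PP as a supportive analysis. Collect the planned questionnaires at both follow-ups from participants who stop the diet, as far as they agree to stay in contact. For scores that are still missing, a likelihood-based model with a sensitivity analysis is one suitable option; the SAP can carry the detail.

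The cost is a change of wording and some follow-up of participants who stop the diet. The estimated effect may be smaller than in the PP set. With 54 per arm the stated 80% power is kept only while dilution stays at or below about 20%. If the sponsor expects more, the sample size should be reconsidered together with its calculation in section 2.11.1.
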